### Study endpoints

The *primary* endpoint of the study is the *feasibility* of the combined intervention as assessed at the post-intervention visit (V4), except in case of compensation sessions, where *feasibility* will be assessed at the end of treatment. To test *feasibility*, we use the following quantitative definition: the intervention is feasible if the probability of a study participant to successfully apply a number of at least 20 out of 30 sessions per protocol exceeds 50%, i.e., it is more likely to receive an adequate dosage of treatment sessions. The threshold of 20 out of 30 treatment sessions is largely based on previous trials of tDCS in MDD, i.e., being close to the tDCS session number in the ELECT TDCS trial and at a higher number of sessions compared to the SELECT trial (22 sessions and 12 sessions, respectively; [26, 27]) to prevent an insufficient dosage of the intervention in this trial. To test this hypothesis, we will determine the quotient of participants successfully completing the intervention according to this criterion relative to the total number of participants. This endpoint was chosen as the primary endpoint due to the novelty of our study design, in which the treatment is performed mostly in a home-based setting. The study has been powered to examine feasibility in the whole sample (i.e., both treatment arms together). In a second step we will estimate confidence intervals for each of the treatment arms separately.

The secondary endpoint is *efficacy,* measured as the change in *MADRS* scores from the baseline visit (V1) to the post-intervention visit (V4). Tertiary endpoints include *clinical response* (at least 50% reduction in the MADRS score from baseline), *remission rates* (MADRS score ≤ 10 points), and *depression relevant status,* assessed via changes in depressive and functional outcomes. Changes on all other assessments from baseline to post-treatment, including *QoL, rumination*, and *cognitive control functions* including *multitasking*, *inhibitory control* as well as *sustained attention* are also included as *tertiary* endpoints*.*

*Exploratory* endpoints include *durability of effects* (i.e., changes on all measures between baseline and follow-up), *expectation for treatment effects* (CEQ scale), *motivation* to participate in the game (IMI scale), and additional domains of cognitive control including the assessment of *WM capacity* and *task switching*.

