### Sample size calculation

Sample size was determined based on the feasibility analysis (primary endpoint). Our primary hypothesis that the probability of completion is larger than 0.5 will be tested using a one-sided binomial test. Assuming *N* = 114 subjects, the one-sided binomial test would reject the null hypothesis (i.e., that the probability of completion is equal or less than 0.5) if the number of completers is ≥ 65 patients. This would constitute an effective completion rate of 57%. In terms of power, if the true completion rate is instead 2/3 (0.67), the probability of rejecting the null hypothesis would amount to approximately 0.98.

This sample size would also adequately power the efficacy analyzes (i.e., time x treatment interaction effect for MADRS change). Power in this analysis was estimated using a Monte-Carlo simulation of 10,000 datasets. Setting the threshold for detection at a significance level of 0.05 (one-sided), the estimated power for *N* = 114 subjects (38 enrolled per site) is 1-β = 0.91. A drop-out rate of 20% was incorporated, based on a comparable ongoing trial at the LMU Munich site [46]. Power measured the probability of detecting a significant time × treatment interaction effect. Effects were estimated using a linear mixed regression model (LMM), with time × treatment and center as fixed effects and subjects modeled as random effects. In the Monte-Carlo simulation, it was assumed that the time × treatment interaction effect was 4 points on the MADRS scale (adapted from [85]). The random effects were set at SD = 6 points for individual change (beyond baseline variability) and a standard deviation of 2.5 points was added as a center × treatment × time interaction. The assumed effect size of the interaction, after controlling for baseline, was Cohen’s *d* of 0.41 (medium effect size).

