### Statistical analysis

For the analysis of the primary endpoint (feasibility and completion rate), we will estimate the probability of completion using the Binomial Fisher’s Exact Test, assuming individuals across centers are independent. Letting *P* be the probability of successful completion (week 6), we will reject the null hypothesis that *P*_(completion)_ ≤ 0.5. A confidence interval for *P*_(completion)_ will be estimated. In a second step, we will estimate the confidence intervals for each of the treatment arms separately.

The analysis of the secondary endpoint (efficacy) consists of an intention-to-treat (ITT) analysis of the change in MADRS scores from baseline to post-intervention by adjusting for inter-individual differences at baseline, sex, and center. A linear mixed regression model (LMM) with random intercepts and center, group, time, and the cross-level group x time interaction as fixed effects will be performed. The key value for significance will be the group × time interaction factor. In case of significant group × time interactions, post-hoc comparisons at each time point with correction of the type-I error probability will be conducted. Confidence intervals for mean differences and effect sizes will be computed. If the analysis at week 6 is found to be significant, an analysis of change over 10 weeks will be performed as a final analysis step concerning the secondary endpoint. All tertiary endpoints will be similarly analyzed using LMMs. Logistic regression will be used to analyze discrete tertiary endpoints (i.e., response and remission rates).

There will be no imputation in the ITT analyzes as the LMMs can handle missing values without excluding entire cases from the analysis. As a sensitivity analysis, LMMs can be computed using state-of-the-art multiple imputation of missing values. At 50% of subjects having completed the study, a planned interim analysis will assess safety and feasibility outcomes. The respective results will be shared with our SMB and published, but will not impact on the conduct of the study, unless major ethical concerns arise.

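### The reason for not imputing covers only the linear mixed models, so response and remission, analysed by logistic regression, would rest on patients with a post-intervention MADRS

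*Protocol article*

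**What the plan says.** All of this is in the protocol article.

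- **Secondary endpoint (Statistical analysis).** "The analysis of the secondary endpoint (efficacy) consists of an intention-to-treat (ITT) analysis of the change in MADRS scores from baseline to post-intervention". The model is an LMM. This is the only endpoint to which the ITT label is explicitly attached.
- **Tertiary endpoints (same section).** "All tertiary endpoints will be similarly analyzed using LMMs", followed at once by the exception: "Logistic regression will be used to analyze discrete tertiary endpoints (i.e., response and remission rates").
- **Missing data (next paragraph).** "There will be no imputation in the ITT analyzes as the LMMs can handle missing values without excluding entire cases from the analysis". Then: "As a sensitivity analysis, LMMs can be computed using state-of-the-art multiple imputation of missing values".
- **Definitions (Study endpoints).** Response is "at least 50% reduction in the MADRS score from baseline"; remission is "MADRS score ≤ 10 points".
- **Expected loss (Sample size calculation).** "A drop-out rate of 20% was incorporated", with 114 patients planned.

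**The concern.** The article makes a positive decision not to impute and supports it with one reason, a property of LMMs. Two of the endpoints described just before are not analysed by LMM. A logistic regression with one outcome per patient cannot use a patient whose outcome is undefined, so it does exclude entire cases, which the sentence says will be avoided. The imputation check does not reach these endpoints either, because it is optional and named for LMMs.

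Response and remission are the efficacy results most easily quoted. If patients who are improving less leave more often, and do so differently by arm, the comparison among those who stay is distorted. The interim MADRS scores that could correct for this would be ignored.

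**Working it through.** **1. Which rule reaches which endpoint**

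| Endpoint | Model | Does the stated reason apply? | Does the imputation check apply? |
|---|---|---|---|
| MADRS change (secondary) | LMM | Yes | Yes, optional |
| Continuous tertiary endpoints | LMM | Yes | Yes, optional |
| Response, remission (tertiary) | Logistic regression | No | Not named |

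**2. How many patients**

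Inputs: N = 114 and drop-out 20% (Sample size calculation). Assumptions: drop-out means no V4 MADRS, and allocation is 1:1 (57 per arm).

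- Lost: 0.20 × 114 = 22.8
- Analysed: 114 − 22.8 = 91.2, or 57 × 0.80 = 45.6 per arm

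**3. What the missing outcomes could do at most**

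The article gives no response rates. Assume 30% (control) and 50% (active) among those observed, with 20% missing in each arm.

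- Complete cases: 0.50 − 0.30 = 0.20
- Missing = non-response: 0.50 × 0.80 − 0.30 × 0.80 = 0.40 − 0.24 = 0.16
- Worst case for active: 0.40 − (0.24 + 0.20) = −0.04
- Best case for active: (0.40 + 0.20) − 0.24 = 0.36

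These are limits, not estimates of bias.

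**4. When complete cases mislead**

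This is a simulation of 400,000 patients, large enough that sampling error is negligible.

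- Taken from the article: a 4-point MADRS difference, an SD of 6 for individual change, and 20% missing V4 overall.
- Assumed: baseline MADRS mean 26 and SD 5; mean V4 improvement 9 (control) and 13 (active); residual SD 3; and, in every row but the first, more drop-out among patients who had improved less by V3.
- Imputation: V4 MADRS drawn from a regression on baseline, V3 and arm with arm interactions, then dichotomised. One draw is enough at this sample size.

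Entries are response rates control / active, with the difference in brackets.

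| Drop-out depends on earlier change | All patients | Complete cases | Imputed, then dichotomised |
|---|---|---|---|
| Not at all | 0.288 / 0.499 (0.212) | 0.287 / 0.500 (0.212) | 0.288 / 0.499 (0.212) |
| Equally in both arms | 0.288 / 0.499 (0.212) | 0.331 / 0.536 (0.206) | 0.288 / 0.499 (0.211) |
| Control arm only | 0.287 / 0.500 (0.212) | 0.349 / 0.500 (0.151) | 0.288 / 0.500 (0.212) |
| Active arm only | 0.288 / 0.500 (0.212) | 0.288 / 0.563 (0.275) | 0.287 / 0.500 (0.213) |
| Equally, plus extra drop-out in active | 0.287 / 0.500 (0.213) | 0.320 / 0.552 (0.232) | 0.287 / 0.501 (0.215) |

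Differences were taken before the rates were rounded.

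The plan's logistic model works on the odds-ratio scale. From the rounded rates, without covariates:

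- Control arm only: complete-case OR = (0.500/0.500) / (0.349/0.651) = 1.87, against (0.500/0.500) / (0.287/0.713) = 2.48 in all patients.
- Active arm only: complete-case OR = (0.563/0.437) / (0.288/0.712) = 3.19, against (0.500/0.500) / (0.288/0.712) = 2.47.

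In the second row the difference is nearly right, but both rates are too high: by 0.331 − 0.288 = 0.043 (control) and 0.536 − 0.499 = 0.037 (active).

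**The case against.** The best defence is that the no-imputation sentence was never meant for the logistic analyses. The ITT label is explicit only for MADRS change, and the reason names LMMs, so the rule may cover only analyses where it is correct. What remains would be silence on two tertiary endpoints in a condensed article whose analysis plan is not shown. The article also says only logistic regression. It does not rule out a repeated-measures logistic mixed model, and no visit is named in the response and remission definitions. "Complete-case" is therefore a consequence of the text, not its wording.

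Part of this stands. It cannot be said that the article plans a complete-case analysis under an ITT label. But the sentence speaks of the ITT analyses in general and directly follows the paragraph that covers both kinds of model. Someone applying it literally would not impute for response and remission and would lose those patients. If a mixed logistic model was intended, saying so settles the point.

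The objection is also right that bias is not inevitable. The first two rows of the simulation show almost none in the difference. Complete-case logistic regression is also consistent when missingness depends only on covariates in the model. And the article does not define drop-out as a missing V4 MADRS.

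A reader might further infer that the multiple-imputation check for the MADRS LMM is empty because it repeats a missing-at-random assumption. The article does not support that. It states no missingness assumption and no imputation model, and both commonly belong in the analysis plan.

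**Conclusion.** The point holds in a limited form. The stated reason for not imputing does not apply to response and remission, and the named sensitivity analysis does not reach them. Read as written, about 23 of 114 patients would drop out of these two analyses, provided that the 20% drop-out means a missing V4 MADRS and that the logistic regression uses one visit per patient.

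The harm is conditional. Under the assumptions above, the response difference moved from 0.212 to 0.151 or 0.275 when drop-out depended on earlier improvement in one arm only. It stayed at 0.212 or 0.206 when drop-out was unrelated to improvement or equally related in both arms. A reader might infer that the efficacy conclusion as a whole is compromised. It is not: both endpoints are tertiary, and neither the primary feasibility test nor the secondary MADRS LMM is touched.

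**What to change.** 1. Limit the no-imputation sentence to the endpoints analysed by LMM.
2. For response and remission, multiply impute the V4 MADRS separately by arm, using the V1 to V3 scores, the MADRS randomisation stratum and center, and then dichotomise. Alternatively, fit a repeated-measures logistic mixed model to all visits. The Study assessments section indicates MADRS ratings from V1 to V5, but the visit schedule (Online Resource 2) is not shown, so V2 and V3 ratings should be confirmed.
3. Show missing = non-response as a check only. With drop-out unrelated to outcome, it shrank the simulated difference from 0.212 to 0.170.

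The cost is a few sentences, a little programming and reliance on an imputation model; no new data are needed. That reliance is real. When drop-out depended on the unseen V4 score itself, imputation gave rates of 0.319 / 0.530 against true rates of 0.288 / 0.500. Complete cases were further off, at 0.359 / 0.560.

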**Fig. 1 Fig1:**
[figure not shown]
Study flow chart

During the *intervention phas*e, both treatment conditions are carried out for a duration of six weeks. In total, 30 treatment sessions are performed daily during weekdays for 30 min per day (15 h of intervention in total). This dose is similar or higher compared to doses used in previous antidepressant trials of tDCS [26, 27, 46] and of CCT [15, 31, 41]. In case of missed treatment sessions, up to four sessions may be compensated for on weekends and up to four sessions may be compensated for in week 7, following the post-intervention assessment after week 6.

The *treatment plan* consists of an on-site period at the clinical center (sessions 1–5; week 1) followed by a home-based intervention under remote supervision (sessions 6–30; weeks 2–6). During the first week, study operators train patients on how to use the combined treatment device. Patients gradually transition to self-manage their treatment based on the instructions and continue from home during the remainder of treatment. On an individual basis, on-site treatment can be extended or abbreviated, based on both the patient's and investigator’s confidence that the treatment can be self-administered at home.

For self-administered home-treatment, patients are supplied with an internet-enabled tablet including the pre-installed video game and tDCS software to support correct electrode positioning and an adequate application of tDCS. Patients are asked to maintain a constant training environment by adhering to the following conditions: adopting an upright sitting position on a chair, minimizing distracting factors such as phones or the presence of other people in the room, and a stable internet connection. Operators provide patients with remote support via telephone or video-call during the home-treatment phase on a per-need basis. In addition, patients are contacted at least once a week, to ensure that treatment is proceeding as planned, as well as to motivate patients for optimal compliance. In addition, study staff continuously monitor session parameters and session completion remotely via a dedicated clinician portal. For safety reasons, the activation of the treatment device by patients outside of the pre-scheduled time slots is disabled.

During the *follow-up phas*e, there are no restrictions in terms of antidepressant treatment strategies; yet any modifications in the treatment plan need to be documented.

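### The plan commits to publishing interim results on the primary endpoint, apparently while later patients are still being treated, which exposes the final feasibility test to avoidable operational bias

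*Protocol article*

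**What the plan says.** The Statistical analysis section of the protocol article states that, once 50% of subjects have completed the study, "a planned interim analysis will assess safety and feasibility outcomes". It continues: "The respective results will be shared with our SMB and published, but will not impact on the conduct of the study", with an exception for major ethical concerns. It gives no date for the publication.

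Feasibility is the primary endpoint (Study endpoints). The criterion is that the probability of a participant "to successfully apply a number of at least 20 out of 30 sessions per protocol exceeds 50" per cent. It is assessed without a comparator: "The study has been powered to examine feasibility in the whole sample (i.e., both treatment arms together"). Under Sample size calculation the hypothesis "will be tested using a one-sided binomial test" against 0.5 with 114 subjects, and the null is rejected "if the number of completers is ≥ 65 patients".

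The Trial design section describes how staff support completion. They contact patients at least weekly, partly "as well as to motivate patients for optimal compliance", and give further support as needed. Up to four missed sessions can be made up on weekends and up to four in week 7, and the on-site phase can be lengthened or shortened for individual patients. Staff also follow session completion continuously through a clinician portal.

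**The concern.** The primary result is a single pooled proportion set against a fixed benchmark. If staff effort or patient motivation changes after the interim result is known, the pooled proportion moves with it, and no concurrent control arm absorbs the change. A halfway figure just under or just over 50% would tell sites how many completers are still needed for a positive trial. The people who could read it are also the people asked to encourage compliance.

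The sentence says the results will not affect conduct, but it pairs that assurance with public release, which works against it. Apart from the exception for major ethical concerns, no decision depends on the feasibility look. Early publication therefore adds exposure without a matching benefit to the trial. At stake is whether the final completion rate can be read as that of one unchanged procedure.

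**Working it through.** **Inputs from the protocol article**
- N = 114, one-sided binomial test against 0.5, success at 65 or more completers, alternative 2/3, stated power about 0.98 (Sample size calculation).
- Interim when 50% have completed the study: 0.5 × 114 = 57 (Statistical analysis).
- Last visit at week 10 (Trial design).
- Recruitment of 2–3 patients per month per site at three sites, i.e. 6–9 per month (Trial design).

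**Assumption.** The documents give no value for a change in completion after release. It is called d here and varied over a range.

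**Step 1: reproduce the plan's figure.** With X ~ Bin(114, 2/3), P(X ≥ 65) = 0.988 (0.990 at a rate of 0.67). This agrees with the stated value of approximately 0.98. With a true rate of 0.50, P(X ≥ 65) = 0.080, which is the baseline for what follows.

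**Step 2: how many patients could be affected.** At the trigger, 57 patients have completed and 114 − 57 = 57 have not. Ten weeks is 10/4.345 = 2.30 months. At 6–9 enrolled per month, 6 × 2.30 ≈ 14 to 9 × 2.30 ≈ 21 patients are then in progress. That leaves 57 − 21 = 36 to 57 − 14 = 43 not yet enrolled.

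**Step 3: chance of passing.** With m patients affected, the number of completers is X = Bin(114 − m, 0.50) + Bin(m, 0.50 + d). The exact convolution gives P(X ≥ 65):

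| d | m = 36 | m = 43 | m = 57 (upper case) |
|---|---|---|---|
| 0 | 0.080 | 0.080 | 0.080 |
| +0.02 | 0.102 | 0.107 | 0.117 |
| +0.05 | 0.142 | 0.158 | 0.191 |
| +0.10 | 0.231 | 0.274 | 0.368 |

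**Step 4: sensitivity.** Time spent on analysis and publication reduces m. With m = 20 and d = +0.10 the chance is 0.15. In the other direction, some patients in progress at the trigger are still under treatment and could also be affected, which moves m from 36–43 towards 57.

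The article states no significance level for the primary test, so the stated cutoff of 65 is used throughout. A cutoff of 67, which the exact test would need for a one-sided 0.05 level, gives 0.037 at d = 0 and 0.13–0.16 at d = +0.10 with m = 36–43. The direction and the relative size of the effect do not depend on which cutoff is used.

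**The case against.** The strongest reply is that publication tells staff little that is new. They follow session completion continuously, unblinded staff receive notices of session events, and data from every game session are reviewed centrally. The coordinating site could count completers at any time. Much of this stands. It limits the added exposure to the formal cross-site result and its public release, and it means that shielding site staff from completion data would be unworkable. It does not explain why the pooled result should be published before the trial ends.

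The support measures also apply to every patient from the start and are part of the supervised intervention under test. That is correct. The concern is a change in their intensity after release, and contact is specified as a minimum frequency, so there is room for it. Such a change has not been shown.

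No publication date is given, and access rules may be set out in the full protocol, which is not shown. Release during the trial is nevertheless the natural reading, because the same sentence goes on to discuss the effect on conduct. If later release is meant, the sentence only needs to say so.

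Three stronger inferences are not supported:
- **Type I error.** A reader might infer that the interim look itself inflates it. It does not, because no early stop for success is planned.
- **Blinding.** A reader might infer that publication weakens blinding for the MADRS. The article does not say that interim safety will be reported by arm, MADRS efficacy is not part of the interim analysis, and raters are separate from treatment staff.
- **Size.** A reader might take 0.37 as the expected chance of passing. It requires all 57 remaining patients to be affected and an assumed shift of +0.10.

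**Conclusion.** The point holds as an avoidable exposure to operational bias in the primary endpoint; bias is not demonstrated. It rests on three stated facts: the interim analysis covers feasibility, its results are to be published, and feasibility is a pooled proportion tested against 0.5 that staff are asked to help raise. It also rests on one inference, that publication precedes the end of treatment for later patients.

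If the true rate is 0.50 and the 36–43 patients not yet enrolled are affected, the chance of a positive primary result rises from 0.080 to 0.10–0.11, 0.14–0.16 or 0.23–0.27 for assumed shifts of +0.02, +0.05 and +0.10. Release after the last patient has finished treatment would largely remove the concern. The change is worth making because it is cheap and early publication serves no decision in the trial.

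**What to change.** Reword the sentence in Statistical analysis so that pooled interim feasibility results, and any safety results by arm, go only to the SMB. State that they will be published after the last patient has finished treatment and assessment. Keep the exception for major ethical concerns.

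Leave routine session monitoring by site staff as it is, since supervised home treatment depends on it. As a check, report the completion rate separately for patients treated before and after the interim analysis.

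The sample size, the cutoff and the power are unchanged. The cost is a delayed interim publication.
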